### Exclusion criteria

Patients with the following characteristics will be ineligible for this study

1. Short life expectancy according to the modified Mizumoto Sore

2. “Radiosensitive” histologies (i.e. lymphoma, SCLC, multiple myeloma)

3. Non-ambulatory status

4. Progressive neurological symptoms/deficit

5. > 3 involved vertebral levels

6. > 2 treatment sites

7. Spine instability

8. Previous radiotherapy at the involved levels

### Treatment planning

#### Patient positioning and imaging

No specific pre-medication will be applied. The patient will be placed in a stable position in the immobilization device (such as Body Fix). For cervical spine lesions, a combination of BodyFix and thermoplastic mask will be used. All patients will undergo a treatment planning CT scan immobilized in the treatment position with reconstruction of 2 mm axial slices. 3D volume imaging will be used for MRI imaging with 0.8-2 mm axial slices. T1 pre- and post-contrast as well as T2 sequences are required. The respective MRI scans will be registered with the treatment planning CT scan using rigid image registration.

#### Target and organs-at-risk delineation

The target volume concept is illustrated in Figure
2.

**Figure 2 F2:**
[figure not shown]
**Concept for definition of the PTV**-**boost and PTV**-**elective and illustration based on three cases with different GTV locations and macroscopic tumor extensions.**

Gross tumour volume (GTV): The target lesion will be outlined on the planning MRI (GTV-MRI) and in cases without MRI imaging on the treatment planning CT scan (GTV-CT).

Planning target volume boost (PTV-boost): The PTV-boost will be based on an anatomical target volume concept, where all macroscopically involved elements of the involved vertebra (body, pedicles, transverse process, spinous process) are defined as PTV-boost.

PTV-elective: Defined as the entire vertebrae of the involved levels.

Organs at risk: The spinal cord will be contoured according to the MRI. A 1 mm expansion of the spinal cord will be performed to account for set-up errors, this being the spinal cord OAR. Additional organs-at-risk to be delineated are pharynx, oesophagus, lungs, kidneys and bowel.

#### Treatment planning

Patients will be treated with a linear accelerator with beam energies varying form 6-18MV. Inversely optimized intensity-modulated radiotherapy will be mandatory. Volumetric modulated arc therapy (VMAT) will be preferably utilized compared to step and shoot IMRT to minimize treatment times.

Two different fractionations will be used depending on estimated life expectancy: patients with long life expectancy (Arm A: Mizumoto score 0–4) will be treated with 10 fractions whereas patients with intermediate life expectancy (Arm B: Mizumoto score 5–9) will be treated with only 5 fractions. Total treatment doses will be 30 Gy and 48.5 Gy at the “PTV-elective” and at the “PTV-boost” for Arm A, respectively. Total treatment doses will be 20 Gy and 35 Gy at the “PTV-elective” and at the “PTV-boost” for Arm B, respectively. Two-Gray equivalent doses (α/β = 10 Gy) at the PTV-boost are 50 Gy and 60 Gy for the 5-fractions and 10-fractions regimen, respectively. The patients will be treated on consecutive workdays, with one fraction per day.

Normal tissue dose constraints are summarized in Table 
1.

**Table 1 T1:** **Organ**-**at**-**risk dose constraints**

	**Maximum dose**			**Mean Dose**	
	**Arm B**	**Arm A**	**Volume of max dose**	**Arm B**	**Arm A**
Fractionation Scheme	5 x 4 / 7	10 x 3 / 4.85		5x 4/ 7	10x3 / 4.85
Spinal Cord + 1 mm	23.75	35	0.1 cm^3^		
Cauda Equina	25	37.5	0.1 cm^3^		
Kidney	-	-		10	12
Bowel	24	37	1 cm^3^	-	-
Esophagus	30	40	1 cm^3^	-	-
Liver		-		12.5	17.5

Normal tissue constraints depending upon the fractionation schema.

#### Treatment delivery

Volumetric cone-beam CT (CBCT) imaging will be obtained at each treatment after patient positioning to verify patient set-up. Another verification scan will be acquired following on-line correction to ensure a residual error of ≤ 1 mm and ≤ 1°, and one following beam delivery to assess for intra-fraction drift.

#### Trial duration and follow-up assessments

The primary endpoint will be pain control assessed 3 months after radiotherapy. Detailed follow-up is outlined in Table 
2. Patient follow-up will continue for five years to evaluate the secondary end points of the trial. Patient accrual is estimated to be finished within 2 years.

**Table 2 T2:** **Patient follow**-**up and assessment scheme**

**Assessment**	**Prior RT**	**weekly during RT**	**Post RT**	**1**-**4 weeks**	**6 weeks**	**3 mon**	**6 mon**	**9 mon**	**12 mon**	**18 mon**	**24 mon**
**Physical Examination**	X	X	X		X	X	X		X		X
**Karnofsky performance index**	X	X	X		X	X	X		X		X
**Documentation of Pain** &**Analgesic Use**	X	X	X	Self assessment	X	X	X	Tel.	X	Tel.	X
**EQ**-**5D**	X	X	X		X	X	X		X		X
**QLQ**-**BM22**	X	X	X		X	X	X		X		X
**NCI CTCAE v4 toxicity**		X	X		X	X	X		X		X
**MRI** / **CT imaging**	X				X	X	X		X		X

Tel: patients will be interrogated by a study nurse via telephone.

Self-assessment: patients will be given letters for self-assessment of pain and analgetic use for the four weeks following radiosurgery.

For evaluation of pain a 10 point visual analogue scale will be used
[15] and analgesic use will be recorded. Pain response is defined as a reduction of ≥ 2 points at the treated site without analgesic increase. Complete pain response is defined as a pain score of 0 at the treated site with no concomitant increase in analgesic intake. Stable pain is defined as unchanged score or within 2 points of the baseline with no increase in analgesia.

Quality of life will be analysed using the EQ-5D and EORTC QLQ-BM22 questionnaires.

Local control will be defined by repeat imaging (preferably MRT or CT). Progression events are defined as radiological documented disease progression using RECIST-Criteria (Revised Guidelines, Version 1.1, 2009)
[30].

Kaplan Meier curves for local tumor control, cancer specific survival and overall survival will be calculated starting from the first day of treatment.

This study will use the International Common Terminology Criteria for Adverse Events (CTCAE) version 4.0 for toxicity and adverse event reporting.

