### Primary endpoint

The primary objective is to determine whether a sustained pain relief can be achieved with dose intensified hypo-fractionated image-guided radiosurgery in patients with vertebral metastasis and intermediate and long life expectancy based on the modified Mizumoto Score. The Mizumoto score is slightly modified to improve overall survival in the group with intermediate life expectancy. Pain response 3 months after radiosurgery will be evaluated as primary endpoint and pain reduction of ≥ 2 points at the treated vertebral site on the 0 to 10 Visual Analogue Scale without analgesic increase will be defined as pain response
[29].

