### Inclusion criteria

Patients with the following characteristics will be eligible for this study

1. Established histological diagnosis of a malignant tumour (primary or metastatic)

2. Vertebral metastasis confirmed via biopsy or radiology

3. Pain in the involved spinal region or free of pain under pain medication

4. Fully consenting patients, > 18 years old

5. Karnofsky Performance Index ≥ 60%

6. Good or intermediate life expectancy according to the modified prognostic Mizumoto Score (score ≤ 9)

7. Patient must be able to tolerate fixation systems and 30 minutes treatment time

8. Discussed in interdisciplinary tumour board

9. The following types of spinal tumours are eligible:

Recurrent / residual tumours after surgery

Tumours in medically inoperable patients or patients deemed inoperable due to limited life expectancy / tumour load

Lesions associated with significant surgical risk

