#### Sample size calculation

This study aims to demonstrate an improvement in pain control at 3 months from approximately 40-50% with conventionally fractionated radiotherapy to 70-80% with image-guided, hypo-fractionated radiotherapy. Assuming an improvement in pain control from 45% to 75% sample size calculations at a 5% statistical significant level show that 27 patients would be required to achieve power of the study of 90%. This is the total number of patients eligible for statistical analysis per study arm, i.e. 54 in total. Considering a 10% drop-out rate, the total number of patients is 60. No comparison will be made between the two study arms.

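### Complete pain response requires no pain reduction, so a patient who enters pain-free and stays so is a complete responder without being a responder

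*Protocol article*

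**What the plan says.** The text below Table 2 of the protocol article (Trial duration and follow-up assessments) gives three pain categories:

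- Response: "Pain response is defined as a reduction of ≥ 2 points at the treated site without analgesic increase".
- Complete response: "Complete pain response is defined as a pain score of 0 at the treated site with no concomitant increase in analgesic intake".
- Stable: "Stable pain is defined as unchanged score or within 2 points of the baseline with no increase in analgesia".

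No order of precedence is given, and complete response is not tied to response. Inclusion criterion 3 reads "Pain in the involved spinal region or free of pain under pain medication", so a baseline score of 0 is allowed and there is no minimum score.

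The Primary endpoint section uses response only: "pain reduction of ≥ 2 points at the treated vertebral site on the 0 to 10 Visual Analogue Scale without analgesic increase", assessed at 3 months. Complete response and stable pain do not appear among the primary, secondary or exploratory endpoints. The Background (section on conventional palliative radiotherapy) nevertheless argues that complete rather than partial response should be the main aim of treatment, and says that conventional radiotherapy achieves it in one quarter of patients.

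**The concern.** A complete response should be the best kind of response. As defined, it is a statement about the follow-up score alone. A patient who is pain-free on medication at entry and still pain-free on the same medication later has shown no change, yet is counted in the category that the Background treats as the real goal. The same patient fails the primary endpoint.

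The trial has no concurrent control, and the Study hypothesis is framed as improvement over historic data. A reader will naturally set the reported complete-response rate beside the one quarter in the Background. If the rate moves with the mix of patients at entry, that comparison says little about the treatment.

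**Working it through.** **1. The plan's own figure, to see whether it is touched.** The Sample size calculation takes 45% against 75%, a 5% level and 90% power, and states 27 per arm. The one-sample normal approximation, two-sided, gives

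n = [(1.960 × √(0.45 × 0.55) + 1.282 × √(0.75 × 0.25)) / 0.30]² = 26.01, rounded up to 27.

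Two arms give 54, and 54 / 0.90 = 60. The figure reproduces. It rests on response alone, so the definitions of complete response and stable pain do not enter it.

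**2. Classifying every score pair.** Take whole-number scores 0 to 10 at baseline and follow-up with no analgesic increase: 11 × 11 = 121 pairs.

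| Category under the printed rules | *within 2* read as ≤ 2 | *within 2* read as < 2 |
|---|---|---|
| Response only | 28 | 36 |
| Response and complete response | 8 | 9 |
| Response and stable | 8 | 0 |
| Response, complete response and stable | 1 | 0 |
| Complete response and stable, not response | 2 | 2 |
| Stable only | 38 | 29 |
| None | 36 | 45 |

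The two pairs that are complete response but not response are 0→0 and 1→0. They are there under either reading of *within*. The nine pairs that are both response and stable (2→0, 3→1, up to 10→8) exist only under the inclusive reading. The number of response pairs is the same either way: 28 + 8 + 8 + 1 = 45 and 36 + 9 = 45.

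**3. Effect on the complete-response rate.** Let f be the share of patients with score 0 at entry, s the share of those still at 0 at follow-up without analgesic increase, and 0.25 the complete-response rate in the others (the Background's one quarter). Then

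reported rate = 0.25 × (1 − f) + s × f.

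The article gives neither f nor s, so both are assumptions. With s = 1, the upper bound:

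- f = 0.10: 0.225 + 0.10 = 32.5%
- f = 0.20: 0.200 + 0.20 = 40.0%
- f = 0.30: 0.175 + 0.30 = 47.5%

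With f = 0.20 and s = 0.60, the rate is 0.200 + 0.120 = 32.0%. The rate exceeds 25% whenever s is above 0.25, and equals 25% for any f when s = 0.25.

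**4. Can complete response exceed response?** Keep s = 1. Pain-free entrants cannot drop 2 points, so the response rate over all patients is r × (1 − f), where r is the rate in painful patients. Complete response is larger when f > (r − 0.25) × (1 − f). For r = 0.45 this is f > 0.20 / 1.20, about 17%. For r = 0.75 it is f > 0.50 / 1.50, about 33%.

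**The case against.** The strongest reply is that nothing the trial formally tests depends on this. The primary cutoff of at least 2 points is stated consistently in both places, and a 2-point drop is a responder whatever else it may be called. A reader might infer from the overlap with stable pain that the primary responder count is ambiguous; the article does not support that. Complete response is not a listed endpoint, and no test against one quarter is planned. All of this stands, and it limits the weight of the point.

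Second, response is defined as at least 2 points in the same paragraph, so *within 2 points* may be meant as what is left over, that is, less than 2. This is a fair reading and would remove the response/stable overlap. It does nothing for 0→0 and 1→0.

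Third, the percentages are a ceiling. Full persistence at 0 is unlikely in metastatic disease: the Background puts the median duration of response to conventional treatment at only 3 to 6 months. This also stands. The figures must not be read as a forecast of what the trial will report.

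Fourth, a fuller protocol or analysis plan may say how pain-free entrants are handled in each denominator. It may, but the definition printed here is explicit, and as written it misclassifies them.

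Patients entering below 2 points also cannot meet the primary endpoint. That is a separate matter and adds no weight here.

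**Conclusion.** The point holds for the definition of complete response. As printed, it is not a subset of response, and together with inclusion criterion 3 it lets patients with no change in pain count as complete responders. The rate therefore depends on the entry mix and cannot be set against the Background's one quarter. The upper bound is 32.5% to 47.5% for assumed pain-free shares of 10% to 30%, given 25% complete response in painful patients and full persistence at 0. With less persistence the figures fall, and the inflation disappears at 25% persistence.

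The overlap between response and stable pain is a minor wording issue that depends on reading *within* inclusively. Neither matter changes the primary responder count or the sample size. This is a defect in descriptive reporting that should be corrected, not a threat to the primary analysis.

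**What to change.** Before results are seen, change the definitions as follows:

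- **Response:** unchanged.
- **Complete response:** a response (reduction of at least 2 points, no analgesic increase) with a follow-up score of 0. It is then a subset of response.
- **Stable:** a change of less than 2 points in either direction, without analgesic increase.
- **Denominator:** report complete and overall response on the same one. Restricting only complete response to baselines of at least 2 would leave the defect in place. For example, take 100 patients, 50 of them pain-free at entry, and suppose 30 of the other 50 drop to 0 and nobody else responds. Complete response would be 30/50 = 60% against a response rate of 30/100 = 30%.
- **Baseline below 2:** report these patients separately, for example as maintained pain-free.

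On the 121 score pairs this gives 45 responses (9 of them complete), 31 stable and 45 with neither, with no pair both response and stable. Compared with the inclusive reading, a rise of exactly 2 points also leaves the stable category (36 unclassified pairs become 45), so the text should say that such rises count as worsening.

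The cost is a few definition sentences. No new data or patients are needed, and the primary endpoint does not change. The downside is a possibly lower reported complete-response rate.

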### Rationale for this trial

The rationale for this trial is based on the same hypothesis as the single-fraction radiosurgical studies: to improve pain control and local tumor control via dose intensified radiotherapy for vertebral metastases. This trial will differ in three important aspects from the currently available literature and trials:

1) A prognostic score for overall survival (modified Mizumoto Score) will be used for selection of patients with favourable life expectancy
[27], who are expected to benefit most from the intensified radiotherapy. The number for treatment fractions will be adjusted based on the modified Mizumoto Score to balance intensity and length of treatment with life expectancy. Selection of patients with long life expectancy will also allow for evaluation of late toxicity and long-term efficacy.

2) Hypo-fractionated radiosurgery with 5 and 10 treatment fractions will be practiced in this study. Based on radiobiological modelling, hypo-fractionated radiosurgery allows higher biologically effective doses to the tumor directly adjacent to the spinal cord than single-fraction protocols. Recurrences at the interface between the spinal cord and the epidural tumor are expected to be reduced by fractionation. This will expand the indications for dose intensified radiotherapy to tumors immediately abutting the spinal cord.

3) Failures in untreated parts of the vertebrae shall be avoided by the use of a simultaneous integrated boost concept. Similar to the single-fraction radiosurgical studies, dose intensification will be performed in the macroscopic tumour using dedicated CT and MR imaging. However, the non-involved parts of the vertebra will be treated with a second dose level (conventional dose) to avoid recurrences in the untreated parts of the vertebrae.

Preliminary results from the University Hospital Wuerzburg with dose intensified irradiation using 20 fractions of 3 Gy
[28] are promising and support the hypothesis of this trial; Patients with long life expectancy were selected for fractionated radiosurgery resulting in an actuarial local control rate and overall survival of 88% and 63% after 2 years
[13]. No acute or chronic toxicity > Grade 2 was seen.

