### Secondary endpoints

1. Local tumor control at the treated vertebral levels and regional tumor control at the neighbouring vertebrae

2. Overall survival and cancer specific mortality

3. Quality of life using the EQ-5D and EORTC QLQ-BM22

4. Acute and late toxicity according to NCI CTCAE v 4.0

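### Kaplan-Meier local control with deaths censored overstates the proportion of patients who fail locally; cumulative incidence should be the reported measure

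*Protocol article*

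**What the plan says.** The estimator is fixed in the protocol article, in the text below Table 2 (Trial duration and follow-up assessments): "Kaplan Meier curves for local tumor control, cancer specific survival and overall survival will be calculated starting from the first day of treatment". The event for local control is given just before it: "Progression events are defined as radiological documented disease progression using RECIST-Criteria". Death is not part of that event.

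Under Secondary endpoints, the first item is "Local tumor control at the treated vertebral levels and regional tumor control at the neighbouring vertebrae" and the second is "Overall survival and cancer specific mortality". The second item is worded as mortality, that is, a risk of dying from cancer, while the analysis text speaks of a survival curve.

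On the time horizon, "Patient follow-up will continue for five years to evaluate the secondary end points of the trial", although Table 2 schedules MRI or CT no later than 24 months. The only outcome figures for local control and survival come from a preliminary single-centre series described under Rationale for this trial, "resulting in an actuarial local control rate and overall survival of 88% and 63% after 2 years".

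The article names no cumulative incidence function or other competing-risk method, and does not write out how deaths are handled in these curves.

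**The concern.** A patient who dies without local progression can no longer progress locally. With progression as the only event, Kaplan-Meier removes that patient from the risk set at death. It then assumes that the patient's later failure rate would have matched that of the patients still followed. The complement of the curve therefore describes local failure in a setting where nobody dies first. It is not the share of treated patients who fail locally.

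In the article's own series 37% of patients had died by 2 years against 12% local failure, so competing deaths are about three times as frequent as the event of interest. A reader who takes 1−KM as the proportion failing will overstate it. Local control is the first secondary endpoint listed. The trial selects patients for life expectancy and aims at durable control in a palliative setting, so how many patients fail locally before they die is the clinically direct question.

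Cancer-specific mortality has the same structure, with deaths from other causes as the competing event.

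**Working it through.** The article states no planning figure for these curves, so there is none to reproduce. The check asks how far 1−KM and cumulative incidence differ under the article's own rates.

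**Inputs**
- Local control 88% at 2 years and overall survival 63% at 2 years (Rationale for this trial; a series treated with 20 fractions of 3 Gy).
- Two-year survival of 40% and 30%: assumptions, to represent higher mortality such as might occur in the intermediate life-expectancy arm. The article gives no survival figure by arm.
- Share f of deaths not due to cancer: not given; assumed 5% to 30%.

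**Model.** Constant, independent hazards. The actuarial 88% is read as a Kaplan-Meier type estimate, and the overall death rate is used as the rate of death without local progression.
- Local failure: λ = −ln(0.88)/2 = 0.0639 per year.
- Death: μ = −ln(0.63)/2 = 0.2310 per year.
- 1−KM(t) = 1 − exp(−λt).
- Cumulative incidence: CIF(t) = λ/(λ+μ) × [1 − exp(−(λ+μ)t)].

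**Local failure at 2 years**
- 1−KM = 1 − 0.88 = 12.0%.
- CIF = 0.0639/0.2949 × (1 − 0.88 × 0.63) = 0.2167 × 0.4456 = 9.7%.
- Excess 2.3 points, ratio 1.24.

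**Higher assumed mortality, same λ, at 2 years**
- Survival 40%: μ = 0.4581; CIF = 0.1224 × (1 − 0.352) = 7.9%.
- Survival 30%: μ = 0.6020; CIF = 0.0960 × (1 − 0.264) = 7.1%.
- 1−KM stays at 12.0%, so the excess is 4.1 to 4.9 points.

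**Local failure at 5 years (extrapolation)**
- 1−KM = 1 − exp(−0.0639 × 5) = 27.4%.
- CIF = 0.2167 × [1 − exp(−0.2949 × 5)] = 0.2167 × 0.7711 = 16.7%.

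**Cancer death at 2 years, overall survival 63%.** 1−KM = 1 − 0.63^(1−f); CIF = (1−f) × 0.37.

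| Assumed non-cancer share f | 1−KM | CIF | Excess (points, before rounding) |
|---|---|---|---|
| 5% | 35.5% | 35.2% | 0.4 |
| 10% | 34.0% | 33.3% | 0.7 |
| 20% | 30.9% | 29.6% | 1.3 |
| 30% | 27.6% | 25.9% | 1.7 |

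**Scale against sampling error.** The binomial standard error of a 12% rate is √(0.12 × 0.88/60) = 4.2 points with 60 patients and √(0.12 × 0.88/30) = 5.9 points with 30. The 2.3-point excess is about 0.56 and 0.39 of these.

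**The case against.** The strongest reply is that Kaplan-Meier local control is a recognised quantity in this field and a legitimate one. The benchmark series is itself reported as an actuarial rate, so a like-for-like comparison needs the same type of estimate. The Discussion also plans dose-effect modelling of recurrences. That concerns the failure rate at the irradiated site, and cumulative incidence would mix in mortality. This stands: it is a reason to keep the Kaplan-Meier curve, correctly labelled. It does not make its complement the proportion of patients who fail.

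A second reply is that the censoring of deaths is inferred and that the full protocol may say more. The inference is close to forced, because the article fixes both the estimator and an event that leaves death out.

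A third is that 2.3 points is well inside one standard error at this sample size. That is true and limits the weight of the point. However, the direction of the bias is known, and more patients would not remove it.

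Readers might also infer more than the documents support:
- **Large overstatement of cancer mortality because overall mortality is high.** Only non-cancer deaths compete with cancer death, and the article does not give their share. If most deaths are from cancer, the bias is slight.
- **A 5-year bias of the size computed above.** Imaging is scheduled only to 24 months, and the calculation carries constant hazards forward from a 2-year result with another regimen.
- **A distorted comparison between arms.** Under Sample size calculation the article rules out comparing them. The size of the bias may differ by arm, but no planned contrast depends on it.
- **A wrong design value for the later randomised trial.** The Discussion says that the methods of selection, target definition, planning and quality assurance will be revised. It does not name the local control rate as a design parameter.

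**Conclusion.** The point holds for local control, at modest size. As specified, 1−KM overstates the proportion failing locally by about 2.3 points at 2 years (12.0% against 9.7%) on the article's own figures, and by 4.1 to 4.9 points if 2-year survival were 40% to 30%. The direction is certain once deaths are censored. The size rests on constant and independent hazards, on rates from a different fractionation, and on an unchanged local failure rate in the higher-mortality scenarios. The 5-year contrast of 27.4% against 16.7% is illustrative only.

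For cancer-specific mortality the bias is real but secondary: 0.4 to 1.7 points at 2 years over the assumed range of non-cancer deaths.

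It would go too far to call Kaplan-Meier local control invalid. It answers a different question from the proportion of patients who fail. The 3-month pain endpoint, the 60-patient total and Kaplan-Meier for overall survival are not affected.

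**What to change.** Amend the sentence below Table 2 to say that local failure is reported by arm as Aalen-Johansen cumulative incidence, with death without local progression as the competing event. Cancer-specific mortality is reported in the same way, with death from other causes as the competing event. Retain Kaplan-Meier for overall survival. Retain Kaplan-Meier local control as a labelled supplement, for comparison with published actuarial rates and for the dose-effect analysis, and state there that deaths without progression are censored. Label any estimate beyond 24 months according to the imaging actually available.

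The change takes one or two sentences and a standard procedure. It needs no new data: progression and survival are already recorded, and cause of death is already required for the cancer-specific endpoint. The downside is a slightly larger set of reported analyses.
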